**Fig 1 pone.0347891.g001:**
[figure not shown]
Tongue _HDS_EMG data processing pipeline. Tongue _HDS_EMG recordings from three patient tasks will be decomposed via DWT, and time-frequency features will be selected using linear discriminant analysis. Voluntary contraction tasks will be decomposed into motor unit spike train estimates using MUEdit, and a CNN will be trained on the resulting MU estimates. A final multitask neural network will make a final CN XII neuropathy prediction from all the data. Abbreviations: _HDS_EMG, High-density surface electromyography; MU, Motor unit; CNN, Convolutional neural network; WL, Waveform length; ZC, Zero crossings; SSC, Sign slope changes; RMS, Root-mean-square amplitude; MAV, Mean absolute value; IAV, Instantaneous absolute value; AMB, Amplitude-modulated bandwidth; FMB, Frequency-modulated bandwidth; SMPSD, Spectral moment of power spectral density; MFD, Mean first derivative of instantaneous frequency; MIF, mean instantaneous frequency; CN XII, Cranial nerve XII.

Relaxation: None are rejected because motion artifacts appear similar to fasciculations on _HDS_EMG.Protrusion: Protrusion task channels will be rejected if the range of the apparent effort curve is larger than 2 standard deviations of the signal mean absolute value.Isometric: Isometric task channels will be rejected if the Pearson’s Correlation of the apparent effort curve shows a non-positive slope or a positive slope with r-squared < 0.2.

All accepted signals are divided into 2-second segments for feature extraction. The Discrete Wavelet Transform (DWT) will be used to extract time series features (waveform length, zero crossings, slope signal changes, root mean square, autoregressive coefficient, mean absolute value, and integrated mean absolute value) and time-frequency features (mean instantaneous frequency, mean first derivative, amplitude-modulated bandwidth, frequency-modulated bandwidth, and spectral moment of power spectral density) [32]. We will perform Mann—Whitney U-tests with α = 0.05 to determine whether these features are relevant to neuropathy through the following comparisons: reduced recruitment vs. no reduced recruitment; polyphasia vs. no polyphasia; increased amplitude vs. no increased amplitude; and increased duration vs. no increased duration. To further demonstrate the clinical relevance of _HDS_EMG features, we will use Pearson’s Correlation Coefficients and multiple regression analysis to express correlations between _HDS_EMG features and tongue functional outcomes (L-ROM and IPOI pressure).

The full dataset will be partitioned patient-wise into 70% for training, 20% for development, and 10% for validation. Features from the training set that discriminate neuropathy severity will be selected using linear discriminant analysis. Missing data may occur during time-frequency feature extraction, as some calculations can trigger divide-by-zero errors, especially for low-frequency components. If this occurs, such examples will be rejected as artifacts. If any class label is represented by less than 10% of the data, recording-wise mean imputation will be performed to augment the number of unique examples in the underrepresented classes.

We intend to train an initial decision tree and support vector machine (SVM), followed by ensemble methods using both trees and SVMs, where possible: Random Forest Classifier, Gradient Boost, and Bagging. We will also train a neural network classifier with a softmax activation function for multiclass classification. Hyperparameter optimization will be performed using 5-fold cross-validation and verified using the development set. To account for potential class imbalance, all ensembled learning methods will be trained using class-weighted sampling to ensure that individual classifiers within the ensemble see class-balanced subsets of the data. Machine learning will be performed using SciKit Learn [33].

The 32-channel _HDS_EMG signals are a convolutive mixture on an _HDS_EMG recording and can be extracted using convolutive blind source separation (BSS). Statistical motor unit decomposition software (MUEdit, Avrillon et al.) [34] will be used to extract estimated spike trains from each suite of voluntary contraction _HDS_EMG tasks. Spike train estimates include valuable MU features such as the number of MUs and discharge rate. We plan to construct shimmer plots for each of the 32 spatial recordings by aligning the identified MU estimate peaks [34]. These aligned MU examples will train a convolutional neural network (CNN), using MU peak morphology to predict neuropathy grade. The CNN will be built with PyTorch and trained with help from Optuna for hyperparameter optimization [35,36].

For the secondary objective, we will estimate the prevalence of neuropathy at three time points (pre-treatment, 3–6 months after treatment, and 18 months to 5 years after treatment), along with exact 95% binomial confidence intervals (CIs). Logistic regression models will be fit with XII neuropathy as a binary response variable adjusted for sampling weights and clinical covariates. For hypothesis 1.1, we will model time as a binary variable (0 = pre-RT and 1 = post-RT), pooling the two post-RT groups (n = 24) versus the pre-RT group (n = 12). Time will be included as a continuous variable (i.e., months pre- or post-RT). We expect an exploratory sample of 36 patients who consent to tongue testing, with equal allocation across 12 patients in one of three groups based on the timing of EMG collection relative to their cancer treatment: pre-treatment, early post-treatment, and late post-treatment. Twelve patients per group ensure a maximum half-width of the 95% CI of 0.29. After treatment, we expect the prevalence of neuropathy to be approximately 40%, based on our published data that 10% of survivors develop clinically detectable neuropathy [9,37]. Unpublished data from the NIH intramural laryngeal study section found that 90% of chronic radiation-associated dysphagia cases have EMG-detectable denervation [38]. The investigators’ data show that 100% of patients with DIGEST grade ≥2 dysphagia who are ≥ 2 years disease-free HNC survivors have EMG detectable neuropathy as early as 2 years post-RT (38% of whom have subclinical neuropathy). Logistic regression on a binary independent variable (pre- vs. post-RT) with a sample size of 36 (n = 12 pre- and n = 24 post-RT) achieves 80% power (α = 0.10) to detect a difference in the probability of neuropathy from 5% pre-RT to 42% post-RT.

### Evaluation criteria

The performance of machine learning classifiers will be divided into two classification settings: binary (CN XII neuropathy vs. no confirmed CN XII neuropathy) and multiclass (neuropathy grade). In binary classifiers, we aim for AUC ≥ 0.70 to support _HDS_EMG as an inexpensive, non-invasive quantitative metric for screening OPC survivors for CN XII neuropathy. Narayanaswami et al. report that electromyographers with 10–20 years of experience have a diagnostic sensitivity of 0.77 and a specificity of 0.71 for neuropathy. [24] This will serve as our benchmark for reliable performance for all binary model development. For the 10% validation set, we will measure model performance simply by the percentage of correctly diagnosed cases of neuropathy. As a secondary validation outcome, we will compare the _HDS_EMG neuropathy severity grade with the gold-standard needle EMG grades.

Multiclass classification will use micro- and macro-F1 scores to evaluate the validity of a refined CN XII neuropathy grade prediction. Saliency mapping for the CNN will reveal which signal regions contribute to each neuropathy grade prediction. Machine learning models will be evaluated using SHapley Additive exPlanations (SHAP) to investigate which features contribute to the model predictions [39].

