**Objective:**

In an exploratory study, examine the feasibility of _HDS_EMG for rapid, non-invasive screening of hypoglossal nerve (CN XII) function and estimate the prevalence of hypoglossal neuropathy before and after oropharyngeal radiotherapy, and associate with patient-reported and clinician-graded functional outcomes. Machine learning performance will be measured through sensitivity, specificity, and F1 score, with a target area under the curve > 0.7 based on literature-reported EMG sensitivity and specificity.

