### Data analysis and machine learning plan

Clinical measures will be used to confirm the diagnosis and grade of neuropathy. We expect a pilot sample size of 36 patients with needle EMG and _HDS_EMG to provide ample statistical power to develop a machine-learning classification algorithm, since acquiring 2 minutes and 20 seconds of EMG data at 10 kHz will yield 50.4 million values (36 pts x 140 sec x 10 kHz). For 32-channel _HDS_EMG at 4 kHz (the threshold for the SAGA device), that is 645.12 million values (36 patients x 140 sec x 4 kHz x 32 EMG simultaneous channels). Still, we acknowledge our limitations in determining the optimal sample sizes, as we do not yet have _HDS_EMG data in OPC patients. If the initial analysis shows insufficient performance, we will assess EMG and _HDS_EMG subsets to further increase the training and test dataset sizes. Fig 1 depicts the general data processing pipeline that will translate _HDS_EMG measures into CN XII neuropathy grade. Signals will be preprocessed using MATLAB R2023a software (MathWorks; Natick, MA). Experimental _HDS_EMG will be denoised using a bandpass filter from 20–500 Hz. The signal quality assessment for each task consists of the following. First, a rolling mean absolute value of each channel (window size 400 samples) will represent the apparent effort exerted by the patient.

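### The AUC target of 0.70 is a bare point estimate with no named model or data partition, so an uninformative signal could meet it with a chance anywhere from about 3% to over 70%

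*Protocol article*

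**What the plan says.** The target appears twice. The abstract's Objective gives it as "with a target area under the curve > 0.7 based on literature-reported EMG sensitivity and specificity". Evaluation criteria restates it, with an inequality that now includes the boundary: "In binary classifiers, we aim for AUC ≥ 0.70 to support _HDS_EMG as an inexpensive, non-invasive quantitative metric". The same paragraph adds a benchmark for binary models from a published study, whose experienced electromyographers "have a diagnostic sensitivity of 0.77 and a specificity of 0.71 for neuropathy". It does not say whether a model must meet both bars or only one.

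The candidate models are in the Data analysis and machine learning plan: "We intend to train an initial decision tree and support vector machine (SVM), followed by ensemble methods using both trees and SVMs" (Random Forest, Gradient Boost and Bagging), then a softmax network and a convolutional network. The Fig 1 caption adds a multitask network that makes the final prediction.

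On data use, the same section says: "The full dataset will be partitioned patient-wise into 70% for training, 20% for development, and 10% for validation". It continues: "Hyperparameter optimization will be performed using 5-fold cross-validation and verified using the development set". Evaluation criteria then scores the 10% set by percentage correctly diagnosed, not by AUC.

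On sample size the plan says: "We expect a pilot sample size of 36 patients with needle EMG and _HDS_EMG to provide ample statistical power". It adds a fallback: "If the initial analysis shows insufficient performance, we will assess EMG and _HDS_EMG subsets to further increase the training and test dataset sizes".

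**The concern.** A target that supports a screening claim should be hard to reach when the signal is useless. This one fixes only the number 0.70. The model, the patients and the number of attempts are open, and each can be settled after the results are seen. With very few patients the AUC takes few possible values and 0.70 is not rare by chance. With several models, the best one reaches it more often still.

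The result would also carry forward. The Discussion says this work will set benchmark sensitivity and specificity values for later sample-size estimates, so a best-of-several figure from a handful of patients would bias the next study towards optimism.

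**Working it through.** **The plan's own figures.** The article gives no error rate or power for the AUC target. Its only formal power figure is for the secondary objective: 80% for 5% versus 42% with 12 and 24 patients at α = 0.10. This reproduces (81% by the pooled two-proportion formula, 82% by the logistic formula), but it concerns prevalence. The claim of ample power for machine learning rests on counts of signal values, such as 36 × 140 × 4,000 × 32 = 645.12 million. The count is right, but these values come from 36 patients.

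**Inputs.**
- Partition: 0.70 × 36 = 25.2, 0.20 × 36 = 7.2 and 0.10 × 36 = 3.6, so about 25, 7 and 4 patients.
- Cases: 12 × 0.05 + 24 × 0.42 = 10.7, about 11 of 36 (30%). Among 7 patients, about 2 cases and 5 non-cases.
- Models: decision tree, SVM, three ensembles and the final multitask network make six. The softmax and convolutional networks make eight, if their grade predictions are collapsed to yes/no.
- Correlation between model scores: not in the article; assumed 0.3 to 0.9.

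**One uninformative model, exact.** Every ranking is equally likely. With 2 cases and 5 non-cases there are 21 rankings, of which 6 have AUC ≥ 0.70: 6/21 = 29%. With 3 and 4 it is 7/35 = 20%. Averaged over the random case count it is about 25%. The two wordings of the target differ here: 2 of the 6 rankings have AUC exactly 0.70, so the abstract's strict inequality gives 4/21 = 19%.

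**Best of several uninformative models, simulated.** Labels were drawn at the 5% and 42% prevalences, a random subset of patients was taken, and each of K models received equicorrelated normal scores unrelated to the label. The figure is the chance that the largest AUC is at least 0.70, given that both classes are present.

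| Patients scored | K | corr. 0.3 | 0.5 | 0.7 | 0.8 | 0.9 |
|---|---|---|---|---|---|---|
| 7 | 6 | 71% | 62% | 54% | 49% | 43% |
| 7 | 8 | 77% | 68% | 58% | 52% | 45% |
| 25 | 8 | 33% | 28% | 23% | 19% | 16% |
| 36 | 8 | 20% | 16% | 13% | 11% | 9% |

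One model gives about 6–7% on 25 patients and about 3% on 36. Separate runs differ by a point or two; the ranges quoted (43–78%, 16–35%, 8–19%) allow for that.

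As a check on the assumed correlations, learners were trained on pure noise with 25 training and 7 development patients. At least one of eight reached 0.70 in 73% of runs, and at least one of six feature-based learners in 60%. Score correlations among the learners mostly lay between 0.3 and 0.8, with one learner uncorrelated with the rest.

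**Effect of the fallback.** Suppose the target is judged again after one round of subset analysis that shares 80% of the common score variance (assumed). The best of eight on 7 patients then rises from 44–68% to 54–80%, at correlations 0.9 to 0.5.

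**Effect of the second bar.** With 2 cases and 5 non-cases, sensitivity 0.77 needs 2/2 and specificity 0.71 needs 4/5. At the most favourable threshold, 3 of 21 rankings meet both: 14% for one model. If both bars were required, the best of eight on 7 patients would fall to 59%, 51% and 38% at correlations 0.3, 0.5 and 0.8, and the best of six to 52%, 46% and 34%.

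**Precision.** The Hanley–McNeil standard error at AUC 0.70 is 0.246 with 2 cases and 5 non-cases, and 0.100 with 11 and 25. In the latter case the lower 95% limit is 0.70 − 1.96 × 0.100 ≈ 0.50.

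**The case against.** A reader might infer that a useless signal would pass more often than not. The documents do not support that as a general statement. It needs four things that the article does not say: that the AUC is judged on the 7-patient development set, that any one model suffices, that score correlations are not very high, and that the sensitivity and specificity benchmark plays no part. On 25 or 36 patients the best of eight stays well below one half. On 7 patients it falls below one half at correlation 0.9.

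The Fig 1 caption may also mean that the multitask network is the one model to be judged. The chance on 7 patients is then 20–29% before any re-analysis. The fallback clause speaks of enlarging the training and test data and does not say that the target is judged again.

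The study calls itself exploratory and words the AUC as an aim. Its stated feasibility criterion is different (more than 80% of recordings meeting quality criteria), and the Discussion allows only exploratory interpretation. A condensed article may also leave model choice and intervals to a fuller plan.

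These points limit the size and gravity of the finding but do not remove it. The article states the target, the split, the metric for the 10% set and the fallback. Taken together they leave the error rate undetermined. The Discussion's caveats concern generalizability (single site, single physician, 36 patients), not chance attainment of the target.

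**Conclusion.** The point stands in limited form. As written, the AUC target has no definite false-positive rate. With no true signal it ranges from about 3% (one model, 36 patients) to over 70% (best of eight, 7 patients, low to moderate correlation), depending on choices that the article leaves open. Even one pre-named model on the development set reaches 0.70 by chance in about 20–29% of cases, so that set cannot carry the claim.

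The exact one-model figures rest only on the case split. The best-of-several figures also rest on the assumed correlations, on patient-level AUC and on the reading that any listed model may qualify. Scoring 2-second segments would not help, since segments from one patient are not independent patients. Severity: should be fixed before the analysis; a stronger grade would not suit an exploratory aim.

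**What to change.** In Evaluation criteria:
- Name one binary model in advance as the one the target applies to, for example the final multitask network in the Fig 1 caption.
- Compute its AUC once, at patient level, from nested patient-wise cross-validation over all 36 patients, with feature selection and tuning inside the loop.
- Report it with a 95% confidence interval. Requiring the lower limit to exceed 0.50 would add almost nothing, since at 11 cases and 25 non-cases an AUC of 0.70 already has a lower limit of about 0.50. The gain comes from one model and all 36 patients.
- State whether the sensitivity 0.77 and specificity 0.71 benchmark must also be met, and use one inequality for the AUC throughout.
- Label the other models, and any subset analysis after insufficient performance, as exploratory and unable to meet the target.

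This needs no new data, only wording and more computing. There are two real costs. A model that does better than the named one cannot be used to claim success. The nested scheme also replaces the fixed 70/20/10 split, including its 10% validation set, or must be reported alongside it.

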## Introduction

Oropharyngeal squamous cell carcinoma, arising from the base of the tongue and tonsil, is increasing in incidence. We now recognize that many tumors are related to the human papillomavirus (HPV), and this trend is expected to continue without decline until at least 2045, despite current vaccination rates [1–4]. Patients with HPV-attributable oropharyngeal cancer (HPV-OPC) tend to have a more favorable survival prognosis than patients with a history of tobacco use [5].

Furthermore, hundreds of thousands of young survivors of HPV-OPC will live a significant portion of their lives with post-treatment toxicities from radiotherapy [1]. Normal tissue injury from radiotherapy along the hypoglossal nerve (cranial nerve XII), such as radiation-induced fibrosis or lymphedema, causes denervation of the tongue musculature, contributing to swallowing dysfunction and increasing the risk of choking and aspiration pneumonia (airway entry of liquids or food) [6–8]. These symptoms significantly decrease survivors’ quality of life (QOL) and, in the worst case, lead to tracheostomy or feeding tube insertion.

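### A pooled AUC near 0.70 does not by itself show that neuropathy is detected in survivors, because radiotherapy status alone could score 0.697 under the plan's own prevalences

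*Protocol article*

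**What the plan says.** The Evaluation criteria section sets the target: "In binary classifiers, we aim for AUC ≥ 0.70", offered "to support _HDS_EMG as an inexpensive, non-invasive quantitative metric for screening OPC survivors for CN XII neuropathy". The abstract's Objective repeats it "with a target area under the curve > 0.7". The binary label is needle-EMG-confirmed neuropathy against none confirmed, with no split by radiotherapy status. The same section adds a benchmark for binary models: sensitivity 0.77 and specificity 0.71, taken from experienced electromyographers.

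The Data analysis and machine learning plan describes the dataset: "The full dataset will be partitioned patient-wise into 70% for training, 20% for development, and 10% for validation". It mentions no restriction or stratification by treatment status. Its secondary-objective paragraph gives the composition: 36 patients, 12 in each of three groups "based on the timing of EMG collection relative to their cancer treatment: pre-treatment, early post-treatment, and late post-treatment". The power statement there is "to detect a difference in the probability of neuropathy from 5% pre-RT to 42% post-RT", with 12 patients before and 24 after radiotherapy. The narrative expectation after treatment is about 40%.

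The Discussion says that time since radiation is not controlled for. It draws the consequence for risk factors, not for the accuracy estimate.

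**The concern.** An AUC is the chance that a randomly chosen case outranks a randomly chosen non-case. If nearly all cases come from the irradiated group, and almost half of the non-cases come from the non-irradiated group, many of those comparisons are between an irradiated case and a non-irradiated non-case. A signal that tracks irradiation wins them all, whether or not it carries information about denervation.

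The screening claim concerns survivors. The Introduction and Discussion describe them as people living with the late effects of treatment. Among them radiotherapy status is constant and has no discriminating value. A pooled AUC could therefore meet the target while saying little about the population in which the tool would be used. The Discussion also intends the resulting sensitivity and specificity to inform later sample sizes, so any inflation would carry forward.

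**Working it through.** **Inputs** (Data analysis and machine learning plan, secondary-objective paragraph): n0 = 12 before radiotherapy and n1 = 24 after; p0 = 0.05, p1 = 0.42; alternative p1 = 0.40 from the narrative. Target AUC 0.70, benchmark 0.77/0.71 (Evaluation criteria).

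**The plan's own figure.** Power for 5% against 42%, 12 against 24, α = 0.10 two-sided:
- Pooled proportion (0.60 + 10.08)/36 = 0.297.
- Null SE = √(0.297 × 0.703 × (1/12 + 1/24)) = 0.1615.
- Alternative SE = √(0.05 × 0.95/12 + 0.42 × 0.58/24) = 0.1188.
- z = (0.37 − 1.645 × 0.1615)/0.1188 = 0.88, so power is 0.81.

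The stated 80% is reproduced, so the inputs are read as the authors meant them. One-sided power would be 0.915 and does not match.

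**A model that knows only radiotherapy status.** Expected counts are:
- Before: 0.60 cases and 11.40 non-cases.
- After: 10.08 cases and 13.92 non-cases.

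Such a model has a single operating point, so AUC = (sensitivity + specificity)/2:
- Sensitivity = 10.08/(10.08 + 0.60) = 0.944.
- Specificity = 11.40/(11.40 + 13.92) = 0.450.
- Pooled AUC = (0.944 + 0.450)/2 = 0.697.
- AUC among the 24 post-radiotherapy patients = 0.50 by construction.

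**Sensitivity to the prevalences:**

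| Before | After | Pooled AUC |
|---|---|---|
| 5% | 42% | 0.697 |
| 5% | 40% | 0.692 |
| 10% | 42% | 0.665 |
| 0% | 40% | 0.727 |

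The AUC equals 0.70 at 43.1% after (with 5% before), or at 4.6% before (with 42% after).

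**Sensitivity to imperfect recognition.** If irradiation is recognised correctly with probability a in both groups, AUC = 0.5 + (2a − 1) × 0.197. At a = 0.9 this is 0.5 + 0.8 × 0.197 = 0.66. At a = 0.8 it is 0.5 + 0.6 × 0.197 = 0.62.

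**Sampling variation.** If one AUC is computed over all 36 patients, the exact binomial chance that radiotherapy status alone reaches 0.70 is 0.62 at 5%/42%, 0.59 at 5%/40% and 0.39 at 10%/42%. A single case can decide it: 0 of 12 and 10 of 24 gives (1.000 + 0.462)/2 = 0.731, while 1 of 12 and 10 of 24 gives (0.909 + 0.440)/2 = 0.675.

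**Precision of the alternative.** Hanley–McNeil standard error at AUC 0.70, with Q1 = 0.70/1.30 = 0.538 and Q2 = 0.98/1.70 = 0.576:
- Post-radiotherapy only, 10 cases and 14 non-cases: √[(0.21 + 9 × 0.0485 + 13 × 0.0865)/140] = 0.112.
- Pooled, 11 and 25: √[(0.21 + 10 × 0.0485 + 24 × 0.0865)/275] = 0.100.

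**The case against.** **The plan does not rest on AUC alone.** The 0.77/0.71 benchmark stands in the same section, and radiotherapy status alone fails it on specificity (0.45 against 0.71). In simulated cohorts of 12 and 24 patients it met both limits in under 0.01%. A reader might infer that the plan's whole yardstick could be passed with information already in the chart. The documents do not support that for the pure yes/no rule. What remains is that the screening statement is attached to the AUC, and the AUC target would not expose the rule.

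**0.697 is a ceiling for that rule.** It assumes perfect recognition of irradiation. Radiotherapy status is not a listed classifier feature, and nothing in the document says how well tongue surface signals separate irradiated from non-irradiated tissue. A reader might infer that the electrodes will pick up fibrosis or lymphedema without denervation. The Introduction says only that injury "such as radiation-induced fibrosis or lymphedema, causes denervation of the tongue musculature", so a signal independent of denervation is a plausible inference and not a stated fact.

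**A timing-only model might seem to score higher still.** Early and late prevalences of 30% and 54% would give 0.76, and 20% and 64% would give 0.81. Both splits are assumptions that average 42% and require perfect recognition of timing. The plan expects prevalence to rise with time but gives no such figures.

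**Pooling over all 36 is inferred.** The plan splits patients 70/20/10, scores the 10% set by percentage correct, and does not say on which set the AUC is computed. The 62% therefore depends on a reading. The expected 0.697 needs only an evaluation set that mixes the groups in the planned 1:2 ratio.

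**The 5% is soft.** It appears only in a power statement for the secondary objective.

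**The term survivors could be read broadly.** The Study design section applies it to the whole care continuum. Even so, a screening tool for radiation-related neuropathy has to discriminate among irradiated patients.

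**Other analyses help in part.** Features are compared with needle-EMG findings and tongue function, and SHAP and saliency maps are planned. As described, none of these is separated by radiotherapy status. The study is openly exploratory, and its explicit feasibility rule concerns signal quality in more than 80% of recordings. This limits the severity.

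**Conclusion.** The point holds in a limited form. Under 5% and 42% prevalence, perfect recognition of irradiation alone gives an expected pooled AUC of 0.697, against 0.50 among survivors. A pooled AUC near 0.70 therefore does not by itself show that neuropathy is detected in the target population. The size depends on a low prevalence before radiotherapy, on how well the signal reveals irradiation, and on an evaluation set that mixes the groups. Within the ranges checked, the AUC runs from 0.62 to 0.73.

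This does not show that the classifier will behave in this way, or that the primary analysis is invalid. It should be fixed, as a matter of which patients the survivor statement is scored in.

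**What to change.** Keep the pre-radiotherapy patients in training. In the Evaluation criteria:
- Base the statement about screening survivors on AUC, sensitivity and specificity from out-of-fold predictions in the post-radiotherapy patients, with confidence intervals. A timing-stratified AUC, which compares only patients within the same timing group, is an alternative.
- Report the pooled AUC beside it.
- Show the AUC of radiotherapy status or timing group alone as a descriptive reference. With about 10 post-radiotherapy cases, a formal requirement to beat it would be hard to justify in an exploratory study.

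The cost is wording and one further analysis of data already collected. The standard error rises from about 0.10 to 0.11. An observed post-radiotherapy AUC of 0.70 would have a 95% interval of about 0.70 ± 1.96 × 0.112, or 0.48 to 0.92. That includes 0.50, so the result should be presented as an estimate and not as a pass or fail.
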